#### Randomization, sample size, and power.

We will use a stratified block randomization allocation to assign girl-BMC dyads to the treatment arm (IMAGE n = 150 or FUEL n = 150) prior to baseline assessment. Power analyses determined that a sample of 300 girls – 150 IMAGE and 150 FUEL is needed to assess efficacy on the primary outcome (STI incidence). Effect size (Cohen’s h) is a function of two proportions defined by Cohen; h = .2 is a small effect, h = .5 is a medium effect, and h = .8 is a large effect. We calculated the power to detect the effect of IMAGE vs. FUEL in reducing STI incidence as measured by having any of three STIs at 12 months post-intervention using a 2-sided test with alpha = .05. The new STI outcome at follow-up was a binary variable (yes/no to testing positive for at least 1 of the 3 STIs), because the study was not powered to examine specific STI outcomes. Based on the IMARA retention rate of 86% for Black female caregiver-girl dyads in Chicago [15], we evaluated the power of STI incidence (yes/no) at 80% retention over 12- months. Based on our previous work, we assume the STI incidence is 25% and 11% at 12 months for girls in the FUEL arm and IMAGE arm, respectively, which is a small-to-medium effect size of h = .37. With the proposed sample size, we will achieve 80% power to detect the intervention effect. We also calculated the standard effect size (Cohen’s d) for group mean comparisons with 80% power for our secondary continuous outcomes, where d = 0 is defined as no treatment effect. We can detect a small-to-medium effect size with the proposed sample size (d = .37).

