#### General statistical issues.

We will use Bonferroni correction to adjust for multiple comparisons as we will analyze multiple outcomes. We will control for Type I error in the analysis of the secondary outcomes but not the primary outcomes to capture important findings that may be obscured from the conservative limits imposed by Bonferroni correction. We will explore whether girls’ sexual behaviors are related to potentially important covariates (e.g., pubertal status) and use regression models to test their effects. To evaluate the impact of Black male caregivers on girls, we will include BMC’s characteristics as covariates in the regression model for girls’ outcomes. We will use a similar approach to evaluate the impact of girls on BMC over time. Missing data will most likely occur because of subject attrition. Based on our intervention studies, we expect 70%-85% retention in both arms. We will evaluate associations between dose (1 vs. 2 sessions) and efficacy. Missingness complicates statistical analyses via biased parameter estimates, reduced statistical power, and degraded confidence intervals. Based on our prior research, we expect minimal missingness in the data collection, but we will consider the item and unit nonresponse. An analysis using only completers is generally valid, assuming data are missing completely at random, but it is inefficient because it discards data points observed for non-completers. We will use all available data and produce valid inferences under the assumption that data are randomly missing. We will quantify the potential bias of these inferences should we suspect missing data to be non-random.

**Compare IMAGE vs. FUEL**^**TM**^

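### The detectable effect for the secondary outcomes (d = .37) matches an uncorrected 5% test, but the plan applies Bonferroni to those outcomes

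*Protocol article*

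**What the plan says.** All references are to the protocol article.

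*Randomization, sample size, and power* allocates "IMAGE n = 150 or FUEL n = 150". For the primary outcome, STI incidence, power is calculated "using a 2-sided test with alpha = .05", and on attrition the section says "we evaluated the power of STI incidence (yes/no) at 80% retention over 12- months". It then turns to "group mean comparisons with 80% power for our secondary continuous outcomes" and concludes "We can detect a small-to-medium effect size with the proposed sample size (d = .37"). That last statement has no significance level, analysed number or retention of its own.

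*General statistical issues* sets the multiplicity rule: "We will use Bonferroni correction to adjust for multiple comparisons as we will analyze multiple outcomes". It then says where the rule applies: "We will control for Type I error in the analysis of the secondary outcomes but not the primary outcomes". On attrition it says "we expect 70%-85% retention in both arms".

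*Aim 1 (Efficacy)* names two secondary outcomes, number of sexual partners and consistency of condom use. *Data reduction and preliminary analyses* adds a composite risk score beside the individual indicators. The treatment comparison is to be made separately at 6 and 12 months as well as combined. The article does not give the Bonferroni divisor.

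**The concern.** The power section attaches 80% power at d = .37 to the secondary outcomes, and the analysis section reserves its stricter significance level for those same outcomes. Nothing in the article says that .37 already allows for the correction. If it was worked out at 5%, the planning figure and the planned test use different levels, and the secondary analyses have less power than the article tells its readers. The missing divisor is not the complaint, since an article may leave that to the analysis plan. The complaint is that a printed figure does not agree with a rule printed in the same document.

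**Working it through.** **Inputs.** 150 girls per arm; 80% retention, so 0.80 × 150 = 120 per arm; expected retention 70% to 85%, so 105 to 127.5 per arm; power 80%; two-sided alpha .05; Bonferroni for the secondary outcomes. The divisor is an assumption: two is the minimum, from the two named secondary outcomes.

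**Formulas.** For two independent means with n per arm:

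- detectable d = (z(1−α/2) + z(0.80)) × √(2/n)
- power at d = Φ(d × √(n/2) − z(1−α/2))

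The noncentral t gives slightly larger d and slightly lower power. Its values are the ones used in the results.

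**Step 1: reproduce the stated figure.** At α = .05 and n = 120, d = (1.960 + 0.842) × √(2/120) = 2.802 × 0.1291 = 0.362 (noncentral t 0.363). Power at d = .37 is 81.8% (t 81.4%). The stated figure is therefore matched, on the conservative side, by the level and retention used for the primary outcome.

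The primary calculation points the same way. Cohen's h for 25% against 11% is 2·asin(√.25) − 2·asin(√.11) = 1.047 − 0.676 = 0.371, and with 120 per arm at 5% this has 82% power. The same inputs serve .37 in both places.

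**Step 2: other readings of .37.** With 150 per arm and no attrition at 5%, the detectable d is 0.324. With 105 per arm at 5% it is 0.387 to 0.389. One corrected reading comes close: 150 per arm at .05/3 gives 0.374 (t 0.375). It ignores the 80% retention and needs a divisor that the article does not state.

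**Step 3: apply Bonferroni for two tests (α = .025).** At n = 120, d = (2.241 + 0.842) × 0.1291 = 0.398 (t 0.400). Across the article's own retention range, by noncentral t:

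| Retention | n per arm | Tests | Detectable d at 80% power | Power at d = .37 |
|---|---|---|---|---|
| 85% | 127.5 | 2 | 0.388 | 76% |
| 80% | 120 | 2 | 0.400 | 73% |
| 70% | 105 | 2 | 0.428 | 66% |
| 80% | 120 | 3 | 0.420 | 68% |
| 80% | 120 | 4 | 0.434 | 64% |

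The rows for three and four tests are scenarios. Three would be the two indicators plus the composite; four would be two outcomes at two time points.

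**Step 4: what would make .37 correct?** For two tests, n = 2 × (3.083)² / (0.37)² = 19.01 / 0.1369 = 138.9, so 139 per arm (about 140 by noncentral t). That is 140/150 = 93% retention. The power section plans on 80%, cites 86% from the earlier mother-daughter trial, and the analysis section expects 70% to 85%. With three tests, even no attrition falls slightly short: 150 per arm gives 0.375, with 79% power at .37.

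**The case against.** **The basis of .37 is inferred.** The sentence states neither alpha nor n, and the 5% level and 80% retention are stated for the primary outcome. This stands, and the point should say that the figure matches an uncorrected test, not that it is known to come from one. The one near match under Bonferroni (150 per arm, three tests) does not rescue the figure, because at 80% retention the same three tests give 0.420.

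**The planned model is not an unadjusted comparison.** Continuous outcomes are to be analysed by linear regression with the baseline outcome as a covariate, which multiplies the detectable d by about √(1−r²). A baseline-to-follow-up correlation near 0.38 would bring 0.400 back to .37, because √(1 − 0.38²) = 0.925 and 0.925 × 0.400 = 0.37. For three tests r would have to be about 0.47. This is fair, and it is why 0.400 should not be called the true detectable effect. But the article gives no correlation, claims no such gain, and describes its figure as a comparison of group means. Clustering within workshops of 6 to 8 dyads would push the other way.

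**The divisor is unknown.** It is also not settled that both named secondary outcomes are continuous. Both remarks are right. Two tests is therefore used as a minimum, and larger divisors are shown only as scenarios.

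**The consequence is small.** The secondary d set neither the sample size nor a decision rule, and a null secondary result would be read from its estimate and confidence interval. This also stands, and it limits the weight of the point.

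**Conclusion.** The mismatch holds in a limited form. The stated d = .37 at 80% power is what an uncorrected 5% test gives at the planned retention, and the plan's own multiplicity rule does not deliver it. For two tests the detectable d is 0.388 to 0.428 across 85% to 70% retention, and power at .37 is about 76% to 66%. This rests on an inferred basis for .37, at least two tests, girls treated as independent and no baseline adjustment.

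A reader might infer more than this, and the documents do not support it:

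- That 0.40 is a floor, or that an effect of .37 would be missed at least 27% of the time. Both hold at 80% retention with two or more tests. At 85% with two tests the values are 0.388 and 24%.
- That .37 survives two tests only if no girl is lost. It survives with a loss of about 10 per arm, though that is still fewer than the protocol expects to lose.
- That the trial is too small. Its size was set on the primary outcome, which is exempt from the correction and whose power is not affected here.

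**What to change.** In *Randomization, sample size, and power*, restate the detectable d for the secondary continuous outcomes at the Bonferroni level that will be used and at the planned retention, and give both with the figure. For two outcomes at 80% retention this could read d = 0.40 at two-sided alpha 0.025 with 120 girls per arm analysed. If the final number of tests is larger, give the value for that number (0.42 for three). If the authors want to rely on baseline adjustment to support .37, they should state the correlation assumed and allow for workshop clustering in the same calculation.

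The cost is one sentence and a slightly less favourable figure. Sample size, design and conduct do not change.

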#### Aim 1 efficacy study conditions.

**Intervention group: IMARA for black male caregivers and girls empowerment (IMAGE)**: IMAGE is an 8-10-hour HIV/STI group-based (6-8 dyads) prevention program delivered to girls and BMC, together and separated, reviewing parallel content. Modules address individual, social, and structural drivers of HIV risk (Table 1). The IMAGE curriculum was tailored specifically for Chicago’s Black girls and male caregivers. The topics discussed in the curriculum include the sexual development of Black girls, the risk of sexual violence, female anatomy, body positivity, HIV/STI knowledge and attitudes, and contraception use. IMAGE was created to foster healthy communication and connection between male caregivers and their girls by encouraging conflict resolution and perspective-taking. Male caregivers learn about the importance of mental health, role modeling, and partner choices. Through IMAGE, male caregivers will become more aware of their presence in their girls’ lives, discuss absenteeism (in the event they are incarcerated or unable to be physically present), and learn to be present. IMAGE emphasizes how Black girls and women are portrayed in the media, which creates unhealthy stereotypes, decreases self-image, and increases vulnerability to sexual violence. Girls and caregivers will discuss intimate partner violence, power dynamics, and healthy relationships, as well as discuss the use of contraceptives, specifically condoms. IMAGE directly addresses structural factors on girls’ HIV/STI risk, namely male incarceration, sexual violence, domestic violence, and negative stereotyping. Woven throughout IMAGE is the impact of mental health, gender-based violence, and alcohol and drug use on HIV risk.

**Table 1 pone.0320164.t001:** IMAGE Curriculum: Theoretical Constructs, Activities, and Target Participants.

Constructs	IMAGE Activities	Target
**Individual-level constructs**		
Sexual development	Becoming a Sexual Black Woman – theoretical framework overview	Joint
	Adolescent development jeopardy – developing body positivity and challenging assumptions	BMC Girls
	Birth control options resource guide and scenarios	Girls
HIV/STI knowledge, attitudes, beliefs and skills	Virus carrier handshake – assessing sexual partners’ risk behaviors	BMC Girls
	LIPSTICK – mnemonic acronym for condom use	BMC Girls
	Drugs and alcohol interactions with sex	Joint
	PrEP for Black women and female condom use	BMC Girls
	Keep It Simple Sister (KISS) – mnemonic acronym for responding to sexual pressure	Girls
	Guess Who – STI contraction, testing, and treatment	BMC Girls
Emotion regulation	Healthy coping with feelings as triggers for risk behavior	BMC Girls
	Destigmatizing mental health strategies for Black male caregivers	BMC
**Social-level constructs**		
BMC-Girl communication, conflict negotiation and effective communication	Role Plays – Passive, aggressive, and assertive communication	BMC Girls
	Role Plays – Different types of communication	Joint
	Discuss protection and navigating conflict between BMC-Girls	Joint
	Rephrase-it Game – Using I statements to communicate emotions	BMC Girls
Bonding, BMC as resources for HIV/STI prevention and protection	Getting to know one another – role plays to develop empathy	Joint
	Compliments for free – BMC-Girl bonding	Joint
	Discuss absenteeism, protection and incarceration	Joint
	The Big Talk – modeling BMC-Girl sex discussion	Joint
**Structural-level constructs**		
Stereotype endorsement and sexual objectification	Positive and negative portrayal of Black men and women in media	BMC
	Young, Black, and female – positive characteristics vs. stereotypes	BMC Girls
	Unpack toxic masculinity	BMC Girls
	Black female stereotypes (historical, media and cultural)	BMC Girls
Justification of violence in partner/relationship and partner dynamics	Gendered role stereotypes in relationships	BMC Girls
	Healthy versus unhealthy relationships, concurrent partnerships	BMC Girls
	Choosing healthy relationships, identifying abuse	BMC Girls
	Partner selection and implications for HIV risk	BMC Girls

BMC = Black male caregivers.

**Control condition: FUEL, a health promotion program**: We used a similar approach as described above (ADAPT-ITT) to tailor FUEL for Black girls and male caregivers in Chicago. FUEL promotes healthy living practices and topics, namely media literacy, healthy eating and physical activity, healthy eating and nutrition, physical activity, teen drug and alcohol use, and violence prevention (Table 2). Like IMAGE, topics are covered in both separate and joint sessions. FUEL has a brief HIV education module, but it does not address SRH dyad communication or conflict navigation. Video essays, documentaries, and information are used to address relevant topics.

**Table 2 pone.0320164.t002:** FUEL Curriculum: Health Promotion Topics.

Topics	FUEL Activities
Media literacy	Media’s influences body image, beauty, and strength
	Digital altering, filters, and social media trends’ impact on self-esteem
	Using personal collage to practice articulating healthier self-image
Healthy eating and physical activity	Combatting common missteps in diet/nutrition
	Benefits of exercise and meditation to overall health and well-being
	Planning physical activities that can be shared between BMC-Girls
Teen alcohol and drug use	Prevalence of drug and alcohol use among teens
	Impacts of drugs and alcohol on teen development
	Resources for harm reduction and smoking cessation
Violence prevention	Types and prevalence of violence (gang, domestic, bullying, dating)
	Localized examples of violence interruption and bystander intervention
	Discuss impacts of gun violence prevalence in Chicago

#### Intervention training.

Facilitators for both conditions must identify as Black, female, and have some experience working with Black communities or families. Facilitators were assigned to deliver IMAGE or FUEL. All facilitators completed 20 hours of training on their assigned curriculum and received supplemental one-hour training in-person and virtually to introduce key themes of cultural competency, PrEP, HIV prevention education, sex trafficking/human trafficking risk awareness, and general drug safety and navigating substance use disorders. Training for both programs stressed the importance of following the manualized protocol to ensure fidelity across facilitators and completing fidelity measurements at the end of each workshop. Following a curriculum review during the first two training sessions, facilitators practiced delivering each activity, taking turns serving as group leaders and participants. Each facilitator was “certified” as competent to deliver IMAGE or FUEL by the principal investigator and project director.

#### Aim 1 efficacy trial.

Six to eight dyads will be assigned to workshops randomized into FUEL or IMAGE at each CBO and will receive the corresponding curriculum on a designated weekend. Four facilitators and two observers are needed for each study condition; facilitators are not to be cross-trained in IMAGE and FUEL. Two facilitators co-lead the girls’ groups, and two co-lead the male caregivers’ groups. All four facilitators co-lead the joint sessions when girls and male caregivers come together for specific activities. Breakfast, lunch, and snacks are provided at all workshops for facilitators and participants.

#### Supervision, quality assurance, and treatment.

We will use a detailed manual and facilitator guide, conduct weekly supervision, and assess fidelity using facilitator self-report and observer ratings of adherence and competence (see below). Adherence measures determine if the program was delivered as intended (yes/no), and competence ratings indicate the quality of delivery. Each workshop is delivered by four facilitators and observed by two trained individuals to ensure fidelity and report on the quality of the workshop. Observers and facilitators will complete surveys after each workshop day, reflecting on the quality of facilitation. Participants will complete workshop evaluations. During ongoing supervision, the IMAGE research team will review fidelity reports and participant evaluations, discuss session activities and problem-solving difficulties, and provide feedback. If facilitators deviate from the curriculum, the supervisor will provide additional training until fidelity is achieved. We will complete observations of at least 40% of study workshops.

#### Contamination.

We will minimize contamination across arms. Facilitators will be assigned to IMAGE or FUEL and will not discuss or learn the other arm’s curriculum; training is done separately. The workshops will not be conducted on the same days; weekends will be divided, and each CBO will have only FUEL or IMAGE weekends to reduce participant contact. Confidentiality and a general orientation to the research structure were emphasized during facilitation training, allowing us to expect limited contamination.

### Intervention: 3-step sequence for implementation aim 2

We will utilize a 3-Step Implementation Model and its implementation guide [33] at each CBO to Prepare, Rollout, and equip them to Sustain IMAGE. The three steps are outlined more in the implementation procedures section.

### Step 1 prepare

Our team has previously developed partnerships with directors at six CBOs. The curriculum is designed to be flexible and capable of being delivered in various community settings. We will conduct site visits with each director, including environmental scans of prerequisite resources for hosting workshops. Each CBO director will appoint an internal liaison to lead recruitment activities and bridge communication between the sites and the IMAGE team, and the project director will interview liaisons to collect qualitative preparedness data. The information will be collected during site visits, interviews, and a brief prep phase survey to write a tailored implementation plan for each site per year. The implementation plan will then act as a living reference to guide workshop scheduling and execution for the year.

### Step 2 rollout

Each CBO hosts an equal number of IMAGE and FUEL workshops for the efficacy study (Aim 1).

### Step 3 sustain

With support and assistance from the implementation team, the CBO will review their experiences and decide if they will continue offering IMAGE at their location.

### Partnering CBO personnel

Each CBO follows the same sequence of steps to Prepare, Rollout, and Sustain IMAGE. The study will began with the Prepare phase, which involved engaging with the CBOs. During Rollout, the efficacy data (Aim 1) is collected across the 3 time points: baseline, 6, and 12 months. Aim 2 will formally evaluate and compare the implementation determinants (barriers, facilitators, constraints) and processes within and across six CBOs using data generated from surveys, observations, study notes, and interviews with CBO liaisons and directors, hereafter CBO personnel. *CBO personnel* (n = 12) will be asked and consented to participate in surveys and qualitative interviews. Each CBO director will select a liaison who is the reference contact for everything related to the workshops. CBO liaisons will oversee recruiting dyads and bridging the CBO and the IMAGE team. Inclusion criteria: All CBO directors (n = 6) and CBO IMAGE liaisons (n = 6) will be eligible. Because CBO liaisons will receive a stipend from UIC and are also CBO employees, we emphasize that participation in the interviews and surveys is completely voluntary. Personnel can refuse to participate without affecting their employment at the CBO or their stipend from UIC. Exclusion criteria: a) inability to understand the consent process, and b) non-employment at a partnering CBO. Regarding CBO personnel turnover (liaisons and/or directors), PI [name] will engage new directors, and directors will appoint a new individual to serve as the liaison and be trained to perform their activities.

#### 
Aim 2 implementation procedures.

During ***Prepare***, we will conduct an environmental scan [37] at each CBO to describe and compare the inner and outer context across CBOs. We will identify structural and logistical resources (i.e., space, furniture, and other infrastructure). The scan also includes documenting current programming, the structure of decision-making, available resources (e.g., staff, space), and client engagement (e.g., number and frequency of the target population coming to the CBO). We review organizational charts to understand staff roles and determine how IMAGE fits the current structure. We identify the needs of each CBO and how the research team can support IMAGE delivery. We work with CBO directors to identify a liaison at the CBO who can interface with the community and assist in recruitment and implementation. We will share the materials related to IMAGE with the CBO personnel - director and liaison from each CBO (n = 12), and we will ask them to complete a survey [38] about the factors likely to affect IMAGE delivery and potential sustainability (ORIC and organizational climate measures). We will also conduct a 45-60-minute semi-structured interview with CBO liaisons (n = 6) involved in the IMAGE study (face-to-face, phone, or via Zoom) to document anticipated barriers and facilitators. The *Prepare* phase semi-structured interview only takes place with the liaison as a follow-up to the conversations held during the initial site visit with the CBO Directors. Verbal consent will be obtained before each interview. Participants will receive a $25 gift card for participating in the interview and survey. After the *Prepare* step, we will triangulate the data to co-create an adaptable implementation plan detailing how to deliver IMAGE at their site.

During IMAGE ***Rollout***, we will complete the Aim 1 efficacy study. After the first IMAGE session, we will dispatch a follow-up survey assessing implementation, adoption, and feasibility and conduct 30-45-minute semi-structured in-depth interviews (in person, by phone, or via Zoom) with CBO personnel (n = 12) to document facilitators, barriers and needed adaptations (e.g., to increase IMAGE enrollment and attendance). Verbal consent will be obtained before each interview, and participants will receive a $25 gift card.

After the trial ends (end of Rollout), CBO personnel will be asked to complete a third survey focused on acceptability, appropriateness, feasibility, and sustainability. We will conduct 45-60-minute semi-structured interviews (face-to-face, by phone, or via Zoom) with CBO personnel (n = 12) to assess each CBO’s total experience and capacity to ***Sustain*** IMAGE. Building on the environmental scan and previous interviews that identified facilitators, barriers, and solutions, we will ask CBO personnel to discuss their ability to integrate IMAGE into current programming. Verbal consent will be obtained before each interview. Participants will receive a $25 gift card.

## 
Study assessments

